[figure not shown]

## Abstract

**Background:** Preterm birth is associated with most cases of neonatal deaths and negative health outcomes, and hypertensive disorders. Hypertension is influenced by maternal behavior, such as physical activity. Physical activity is associated with better outcomes for mother and fetus, besides healthier weight gains during pregnancy. Few women are physically active during pregnancy and few clinical trials have been carried out with pregnant women. The aim of this paper is to describe the protocol of a controlled trial evaluating whether regular exercise during pregnancy may result in improved maternal-child health and neonatal outcomes.

**Methods/Design:** The PAMELA (Physical Activity for Mothers Enrolled in Longitudinal Analysis) trial is a randomized controlled trial nested in a birth cohort study. Eligible women belonging to the birth cohort will be invited (between the 16th and 20th week of gestation) to enroll in the trial. Baseline data (blood and urine samples, anthropometry and pulmonary function) will be collected at enrollment. The same assessments will be repeated eight and 16 weeks after baseline. After randomization, women will be allocated into either one of these groups: control, 426 women who will be advised to keep their usual daily activities; and intervention, 213 women who will engage in an exercise program, three sessions a week. At least 70 % attendance over 16 weeks will be required to be considered compliant to the intervention. Exercise protocol will include aerobics, strength and flexibility training. Maternal and child outcomes will be measured at the 36th week of gestation, at birth and at three, 12, 24 and 48 months postpartum. An intention-to-treat analysis will be performed.

**Discussion:** Few women are active during pregnancy and a vast majority decrease their activities or even quit exercising. We present a population-based regular exercise intervention focused on the prevention of hypertension, pre-eclampsia and preterm birth. Data on the underlying cohort will allow future analysis using different outcomes with low probability of recall bias or misclassification of exposure status. Results will potentially influence prenatal care counseling in regards to physical activity.

**Trial registration:** Clinicaltrials.gov identifier: NCT02148965, registered on 22 May 2014.

## Background

The World Health Organization estimates that over 10 % of births worldwide are preterm [1]. Based on previous population studies in the city of Pelotas (Brazil), the preterm birth rate is increasing (from 6.3 to 14.7 % between 1982 and 2004) [2]. Preterm birth is associated with most cases of neonatal deaths and negative consequences throughout childhood and adult life [3, 4].

Among the strongest predictors of preterm birth are hypertensive disorders of pregnancy [5–7]. Evidence suggests that preterm birth and gestational hypertension risk may be altered by regular leisure-time physical activity [8–12]. The potential hypothesis for such a mechanism is based on reduction in blood pressure, improvement in blood lipids profile, reduced oxidative stress and inflammation reduction [13–15]. Studies also have shown that leisure-time physical activity during pregnancy is associated with lower risk of excessive weight gain [16] and better psychological health [17, 18]. Although evidence supports the benefits of physical activity during pregnancy, few women in Brazil are active during gestation, and the level of leisure-time activity decreases as pregnancy advances [19]. Further, the effect of physical activity on mother-child health outcomes is not fully understood.

With respect to different outcomes, such as diabetes, trials during pregnancy do not provide enough evidence that exercise is effective [20]. The main goal of conducting a trial in the Brazilian population is because physical activity among Brazilian women is highly associated with socioeconomic status and other characteristics not easily controlled statistically during analysis. This trial will allow for the balance of such potential confounders, as we are using a population-based sample and random allocation. Moreover, few experimental studies have been carried out to study such associations in large samples.

## Rationale

Although early studies on the effects of leisure-time physical activity during pregnancy were concerned about potential harmful effects to the health of the mother and the fetus, these have not been proven over time [21]. Current guidelines suggest that pregnant women should engage in at least 30 min of moderate-intensity physical activity on most, if not all days of the week, in the absence of medical or obstetric complications, in agreement with the recommendations for healthy adults [22].

Today, there is growing evidence supporting the association of safe physical activity during pregnancy with benefits to maternal and child health [23, 24]. However, most of the scientific evidence derives from observational studies, and there is a need for well-designed experimental studies that enable a better understanding on the impact of exercise during pregnancy on various maternal and mother-child health outcomes.

## Aim

The aim of this study is to present the experimental protocol of a trial aimed at evaluating the effectiveness of an exercise intervention, by comparing the intervention and control groups with infant outcomes assessed later in life. Data will be collected on: prematurity, gestational age, gestational weight gain, blood pressure, fasting blood glucose, postpartum weight retention, postpartum depression and birth weight.

## Methods/Design

### Study design

A randomized controlled trial will be carried out and eligible women will be sampled from the 2015 Pelotas (Brazil) Birth Cohort Study. Currently three birth cohorts (1982, 1993 and 2004) are ongoing in the city of Pelotas (southern Brazil), each with more than 4,000 subjects that were enrolled soon after birth (at hospital). The 2015 Pelotas Birth Cohort Study recruits pregnant women from health services to begin gathering data prospectively during the prenatal period. More than 3,500 women are expected to be included in the study, providing information on several health-related aspects. All women with an expected delivery date from 1 January to 31 December 2015 are eligible to be included in the cohort.

### Ethical considerations

The clinical trial protocol and the 2015 Pelotas Birth Cohort Study were submitted to the Physical Education School Ethics Committee and were approved under the numbers 649.244 and 522.064, respectively. Also, the following procedures will be followed: Participation in the study will only occur only after reading and signing the consent form; All women will be guaranteed the right to not participate in the study; We will ensure confidentiality of the collected data and document numbers (identifications, used to link databases); and Women presenting health problems during the study will be referred to appropriate health services.

The study is also registered on the Clinicaltrials.gov website under the registry number NCT02148965, entitled 'Effects of exercise during pregnancy on maternal and child health: a randomized clinical trial (PAMELA)'.

### Recruitment and participants

All locations where pregnant women would potentially seek assistance during pregnancy, such as medical laboratories, ultrasound clinics, polyclinics, public primary health units, hospitals, university clinics and private obstetric and/or gynecological clinics, are being visited daily since April 2014 to identify eligible women. Based on the first prenatal interview, those women who meet inclusion criteria will be invited (by a standard phone contact) to participate in the randomized controlled trial. The recruitment

will continue during the prenatal study until we achieve the required sample size. Fig. 1 displays the study design.

### Randomization

Pregnant women meeting the inclusion criteria and who agree to participate in the randomized controlled trial will be allocated randomly into either the intervention or control group. The randomization process will be done in blocks of nine women using random software sampling. Each block will therefore result in the allocation of three women for the intervention and six women for the control group, ensuring a recruitment balance of 1:2 throughout the study. This ratio was chosen as it would minimize costs and behavioral changes in women from the remaining cohort, whilst assuring that statistical power would be unaffected. As the cohort is an observational study, our option was to expose the lowest possible number of women to the intervention. After randomization, women will be allocated into either one of these groups: control, 426 women who will keep their usual daily activities; and intervention, 213 women who will engage in a physical activity program, three sessions a week.

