### Logistics and setting

The study begins with one initial contact with the mother, prior to the 16th week of gestation, when interviewers ask for contact information, conduct a brief interview and hand a leaflet explaining the controlled trial. After enrollment in the study, women will be invited to go to the Epidemiology Research Center to collect baseline data, that is, blood and urine sampling, anthropometry, blood pressure and lung function. The same assessments (in both groups) will be repeated at eight and 16 weeks

after baseline. The facilities of the Federal University of Pelotas at the Physical Education School will be used for the intervention. A second interview at hospital will take place soon after birth (when children will be measured and mothers will be asked about many aspects of their pregnancy). After these initial data collections, when children are three, 12, 24 and 48 months, interviews will be carried out at the Epidemiologic Research Center or the participant's household. Fig. 2 shows the recruitment flowchart and subsequent data collections.

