### Intervention procedures: exercise protocol

The intervention will start between the 16th and 20th week of gestation and will last 16 weeks. Workouts will be guided and supervised by a team of five previously trained physical education professionals. A set of exercises will be suggested for each workout, involving aerobic activities (treadmill or stationary bike), strength training (dumbbells, machines or elastic bands) and floor exercises. The intensity of the exercises will be set according to each woman's perceived effort (within the range of 12 to 14 on the Borg Scale) [25], and will be altered according to the progress of pregnancy. The workload will change according to the week of the intervention, and the stages are described in Table 2.

Each session will last around 60 min, and will include aerobic exercises (treadmill or stationary cycling), strength training (with focus on major muscle groups and pregnancy-specific exercises to help alleviate low back pain, and work abdominal and pelvic floor muscles to prevent urinary incontinence) and will end with stretching exercises. The exercises are described in the Table 3.

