### Control group

Women allocated to the control group will be instructed to continue their usual routines, will do the same assessments as the intervention group and will be followed by the 2015 Pelotas (Brazil) Birth Cohort Study.

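### The fixed, disclosed block of nine split 3:6 makes up to 21% of allocations certain in advance if women are allocated one by one and staff can track earlier allocations

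*Protocol*

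**What the plan says.** The Protocol's Randomization section fixes both the block size and its composition: "The randomization process will be done in blocks of nine women using random software sampling", and "Each block will therefore result in the allocation of three women for the intervention and six women for the control group". The stated purpose is "ensuring a recruitment balance of 1:2 throughout the study". The planned arms are "control, 426 women who will keep their usual daily activities; and intervention, 213 women". Eligibility and agreement come before allocation: "Pregnant women meeting the inclusion criteria and who agree to participate in the randomized controlled trial will be allocated randomly". The section does not say whether women are drawn one at a time or nine at a time.

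The arms differ visibly. In the intervention arm, "Workouts will be guided and supervised by a team of five previously trained physical education professionals" (Intervention procedures). In the other arm, "Women allocated to the control group will be instructed to continue their usual routines" (Control group). After enrolment, "women will be invited to go to the Epidemiology Research Center to collect baseline data" (Logistics and setting), and the exercise takes place at the Physical Education School. Women are identified at many health services and then invited by a standard phone contact (Recruitment and participants). The Abstract places that invitation between the 16th and 20th week. Trial status describes recruitment as ongoing, from September 2014 to an expected end in September 2015.

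**The concern.** In a block of known size and composition, the rest of the block is determined once all three intervention places or all six control places are used. Here both figures are printed in a document issued while women were still being recruited. The arms cannot be masked, so earlier allocations can become known to staff.

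Foreknowledge matters because entry has some slack in time. An invitation or visit can fall anywhere in a window of several weeks, so moving one call by a few days can change a woman's place in a block or put her in the next one. If 639 women enter evenly over about 52 weeks (an assumption), 639 / 52 = 12.3 join per week and a block of nine closes in about 9 / 12.3 × 7 = 5 days. Good faith would not prevent this: adherence requires at least 34 sessions (Follow-up and compliance), so steering willing women towards exercise places could seem helpful.

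The Background says physical activity in this population is tied to socioeconomic status and to other characteristics that are hard to control statistically, and that random allocation is meant to balance them. Any imbalance from foreknowledge would fall on the characteristics that adjustment is least able to repair.

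**Working it through.** **Inputs (Protocol, Randomization).** Block size 9; 3 intervention and 6 control per block; 213 and 426 women, 639 in total.

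**1. The plan's own figures.** 639 / 9 = 71 complete blocks; 71 × 3 = 213 and 71 × 6 = 426. The arm sizes reproduce exactly.

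**2. Certain allocations per block.** Assume one-by-one allocation, a known block size and visible earlier allocations. An allocation is certain when one arm's places are already used up, so the number of certain allocations is the length of the run of same-arm allocations that ends the block.
- Certain control allocations: the 3 intervention women create 4 gaps, and the 6 controls fall into them evenly on average, so 6/4 = 1.5 controls follow the last intervention woman.
- Certain intervention allocations: by the same argument, 3/7 = 0.43 intervention women follow the last control.
- Sum: 1.5 + 0.4286 = 1.93 of 9, or 21.4%.

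Enumerating all C(9,3) = 84 orders gives the same result: 162 certain allocations in total, and 162 / 84 = 1.93. The last woman of every block is always certain, and in half of the blocks two or more women are.

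**3. Scale over the trial.** 71 × 1.93 = about 137 of 639. Of these, 1.5 / 1.93 = 78% are to control. By arm, 1.5 / 6 = 25.0% of controls and 0.43 / 3 = 14.3% of intervention women are foreseeable.

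**4. Predictability short of certainty.** Guessing the arm with more places left in the block is right for 72.8% of allocations. Always guessing control is right for 66.7%.

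**5. Other arrangements.** The third row is a simulation of 639-woman trials. Its sizes are assumed equally likely, and its observer knows the possible sizes and sees every past allocation.

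| Arrangement | Certain in advance | Best-guess accuracy |
|---|---|---|
| Fixed block of 9, one by one, history visible | 21.4% | 72.8% |
| Fixed block of 3, same conditions | 44.4% | 77.8% |
| Random mix of 6, 9 and 12 | about 2% | about 72% |
| Nine enrolled women drawn as one batch | 0% | 66.7% (always control) |

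Depending on batching and concealment, the certain share under the plan as written lies between 0% and 21.4%.

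**The case against.** The strongest reply is that 21% is a ceiling that rests on three conditions: one-by-one allocation, recruiting staff who know the block size, and recruiting staff who see earlier allocations in order. Publication makes the second easy to meet. The Protocol does not settle the other two, and its mention of software sampling from blocks of women can be read as drawing three from nine already enrolled. This stands, and the figure is given as conditional for that reason.

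A reader might infer that staff do foresee one allocation in five in an open-label, single-site trial, or that recruiters are bending borderline self-reported eligibility criteria. The documents do not support either. Neither label appears in the Protocol. Women are identified at many services across the city, and baseline and exercise take place in different facilities. The health interview that settles eligibility happens at first contact, before the 16th week, and therefore ahead of the phone invitation and allocation. Nothing shows that those interviewers know where a block stands. The more plausible routes are whom staff invite and when.

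Three further points have weight. Most foreseeable allocations are to control, which is the default guess anyway. The gain from tracking is about six percentage points (72.8% against 66.7%). Varying the block size hardly changes that accuracy against an observer who sees everything, so concealment carries most of the protection.

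It can also be said that fixed blocks are ordinary, and that custody of the list may be set out in another document. Both are true, and silence about custody is not the finding. What the Protocol does state is one block size and one composition, disclosed during recruitment to an unmaskable trial, and a better choice costs little.

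**Conclusion.** The point holds as a conditional weakness of the stated design. Under one-by-one allocation with a known block size and traceable history, up to 21.4% of allocations (about 137 of 639, 78% of them to control) are certain in advance. If nine enrolled women are drawn together, or if past allocations are truly hidden from those who invite and enrol, the figure is zero.

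A reader might go further and conclude that selection bias has occurred or that the confounder balance is already broken. The Protocol gives no evidence of that, and no bias in any outcome can be estimated from it. The supportable conclusion is an avoidable risk to the property for which the trial was randomised, with a size between none and about one allocation in five.

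**What to change.** For the women still to be randomised:

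- Generate a new list with randomly varying block sizes in the same 1:2 ratio, for example 6, 9 and 12. Avoid blocks of 3, which are the most predictable of the sizes examined.
- Withhold the block sizes from recruiting, baseline and training staff.
- Release each allocation only after consent and baseline assessment are recorded.

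The second and third steps matter at least as much as the first, because varying the sizes removes most certain allocations but leaves best-guess accuracy near 72%.

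If blocks are in fact batches of nine women already enrolled, state that in the Randomization section instead; no new list is then needed.

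The cost is a new list and no extra staff. The final split may depart from 1:2 by a few women. The Protocol does not say how many women remain to be randomised, so the number who would benefit is unknown.

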### Exclusion criteria

During the first contact, women will be interviewed about several aspects of their overall health, and those presenting any of the conditions described in the Table 1 will not be eligible for the trial.

### Logistics and setting

The study begins with one initial contact with the mother, prior to the 16th week of gestation, when interviewers ask for contact information, conduct a brief interview and hand a leaflet explaining the controlled trial. After enrollment in the study, women will be invited to go to the Epidemiology Research Center to collect baseline data, that is, blood and urine sampling, anthropometry, blood pressure and lung function. The same assessments (in both groups) will be repeated at eight and 16 weeks

after baseline. The facilities of the Federal University of Pelotas at the Physical Education School will be used for the intervention. A second interview at hospital will take place soon after birth (when children will be measured and mothers will be asked about many aspects of their pregnancy). After these initial data collections, when children are three, 12, 24 and 48 months, interviews will be carried out at the Epidemiologic Research Center or the participant's household. Fig. 2 shows the recruitment flowchart and subsequent data collections.

### Intervention procedures: exercise protocol

The intervention will start between the 16th and 20th week of gestation and will last 16 weeks. Workouts will be guided and supervised by a team of five previously trained physical education professionals. A set of exercises will be suggested for each workout, involving aerobic activities (treadmill or stationary bike), strength training (dumbbells, machines or elastic bands) and floor exercises. The intensity of the exercises will be set according to each woman's perceived effort (within the range of 12 to 14 on the Borg Scale) [25], and will be altered according to the progress of pregnancy. The workload will change according to the week of the intervention, and the stages are described in Table 2.

Each session will last around 60 min, and will include aerobic exercises (treadmill or stationary cycling), strength training (with focus on major muscle groups and pregnancy-specific exercises to help alleviate low back pain, and work abdominal and pelvic floor muscles to prevent urinary incontinence) and will end with stretching exercises. The exercises are described in the Table 3.

### Primary outcome measures

Preterm birth (gestational age below 37 weeks of pregnancy), and pre-eclampsia (blood pressures above 140/90 mmHg and proteinuria above 15.0 mg/dL) will be assessed during pregnancy and soon after birth.

[figure not shown]

**Fig. 1** Study design

**Table 1** Exclusion criteria of the randomized controlled trial

| Exclusion criteria            | Description                                                   |
|-------------------------------|---------------------------------------------------------------|
| Age                           | Below 18 years                                                |
| Hypertension                  | Diagnosed before pregnancy/Self-reported                      |
| Diabetes                      | Diagnosed before pregnancy/Self-reported                      |
| Preterm birth                 | History of previous preterm birth                             |
| Miscarriage                   | History of previous miscarriage                               |
| Heart disease                 | Diagnosed before pregnancy/Self-reported                      |
| In vitro fertilization | Fertilization in the current pregnancy                        |
| Double/twin pregnancy         | Twin pregnancies confirmed by ultrasound                      |
| Persistent bleeding           | Women presenting persistent bleeding                          |
| Severe obesity                | Body mass index above 35 kg/m                     |
| Heavy smokers                 | Smoking more than 20 cigarettes a day                         |
| Active women                  | Weekly leisure-time physical activity > 150 min/Self-reported |

